#### Identify Treatment Received During IETP

Consistent with prior studies [50-52], we will create an abstraction tool in collaboration with IETP clinicians and aim 1 data. Using the crosswalk database, we will conduct chart abstraction for IETP focusing on the initial assessment, TBI care plan, processes and amount of care received, discharge assessment, and TBI care plan. After finalizing the procedures and appropriate training, team members will independently review 10 charts and then meet to identify inconsistencies, errors, or disagreements and resolve any by consensus. This will continue until there is 90% agreement on all items abstracted, to ensure abstraction fidelity. The areas of uncertainty will be discussed with IETP clinicians. These data will be merged with IETP data, VA and DoD analytic file data, and survey data for the outcome analyses.

We will identify what happens during the IETP stay using descriptive statistics for the overall cohort, stratified by phenotypes from the measures listed in the *Measures and Data Collection Procedures* section. We expect that different types of care will be provided to individuals with different prior comorbidities and clinical presentations. We will apply Pearson chi-square test to assess the association between recommendations for admission TBI care plan and TBI phenotype.

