## Abstract

**Background:**

The traumatic brain injury (TBI) Intensive Evaluation and Treatment Program (IETP) is an innovative modality for delivering evidence-based treatments in a residential, inpatient format to special operational forces service members and veterans with mild TBI. IETPs provide bundled evidence-based assessment, treatment, referral, and case management in concordance with the existing guidelines for mild TBI and commonly co-occurring comorbidities. To date, there has been no formal characterization or evaluation of the IETP to understand the determinants of implementation across the system of care. The goal of our partnered evaluation initiative (PEI) with an operational partner, the Physical Medicine and Rehabilitation National Program Office, is to facilitate the full implementation of the IETP across all 5 Veterans Health Administration TBI–Centers of Excellence (TBI-COE) and to inform minimum standards while supporting the unique characteristics of each site.

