### TBI IETP—Innovative Modalities of Care

Innovative modalities of care improve access to evidence-based care for mild TBI. Innovative models of care have been developed within the polytrauma system of care, which includes 5 specialty TBI-COE that provide comprehensive rehabilitation services for veterans and service members with TBI. The TBI IETP is an innovation that has yielded high consumer demand across locations. The IETP delivers evidence-based care in a residential, inpatient format. The IETP provides bundled evidence-based assessment, treatment, referral, and case management in concordance with the existing guidelines for mild TBI and commonly co-occurring comorbidities (refer to the IETP characterization table in Multimedia Appendix 1 [4-23]). Indeed, the residential format has grown out of necessity to address the unique needs of the SOF population in a compressed, timely manner ideally suited for abbreviated inpatient treatment stays. A recent study by Dismuke-Greer et al [24] highlighted higher annual outpatient use and cost over protracted time intervals for veterans with mild TBI compared with non-TBI controls, highlighting extended intervals and delayed access to evidence-based care. Proponents of IETP emphasize its improved access to evidence-based care, including TBI-adapted treatment of mental health conditions previously published [25,26].

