#### Identify Components of IETP Associated With Sustainment and Improvement Trajectories

Outcomes currently identified by operational and clinical stakeholders that are collected at all sites (Tables 3 and 4) will be included in the survey to develop longitudinal outcome trajectories. On the basis of stakeholder feedback, we will also measure and describe community reintegration, employment, retention in the military where relevant, compliance to discharge from the TBI care plan, reasons for difficulty in care plan compliance, and unmet rehabilitation needs. Per operational partners’ request, we will also use VHA and DoD data to identify use relevant to discharge (eg, TBI care plan within primary, mental health, specialty care, or emergency care).

We will use Bayesian network analysis to generate a directed acyclic graph, which probabilistically describes the trajectory of symptoms, care, and outcomes for IETP participants. This network will enable us to explore the contribution of the baseline phenotype to the decision to use a particular treatment course and the contribution of those treatments to the participants’ resulting outcome measures [53]. Using a hill-climbing algorithm scored with the Bayesian information criterion, we will establish directional connections between nodes, called edges, and evaluate the robustness of the edges using bootstrapped samples of the data. We will a priori exclude any implausible directed edges (eg, IETP care cannot lead to precare symptoms). The resulting directed network will have edges between the levels: (1) phenotypes, (2) treatment, and (3) outcomes, while disallowing connections that go from levels 2 to 1 or 3 to 2 or 1. We can allow edges between nodes within the treatment level of the network to better understand the interactions between treatments and to assess how the treatments individually and in combination probabilistically affect patient outcomes. By fitting this model, we can isolate the most probable trajectories between TBI phenotypes and treatments and then determine which treatments have a higher probability of positive long-term outcomes. To gain an understanding of the treatment courses on outcomes, we will present a graphical display of the nodes and edges, the conditional probabilities calculated between nodes that estimate the probability of long-term outcomes given the participants’ IETP components and comorbidity phenotypes, and the robustness measures from bootstrapping.

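### The 90% raw-agreement gate for chart abstraction cannot establish reliability for any component that nearly every patient receives

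*Protocol article*

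**What the plan says.** The section Identify Treatment Received During IETP describes an abstraction tool built with clinicians. After training, "team members will independently review 10 charts and then meet to identify inconsistencies, errors, or disagreements and resolve any by consensus". The stopping rule is "This will continue until there is 90% agreement on all items abstracted, to ensure abstraction fidelity". Uncertain points get a further step: "The areas of uncertainty will be discussed with IETP clinicians".

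The abstracted items then feed the main quantitative work: "These data will be merged with IETP data, VA and DoD analytic file data, and survey data for the outcome analyses". In the Bayesian network section, treatment nodes are used to "determine which treatments have a higher probability of positive long-term outcomes". The Abstract and the Conclusions say that ineffective components will be targeted for deimplementation.

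The program is described as a bundle: "The IETP provides bundled evidence-based assessment, treatment, referral, and case management in concordance with the existing guidelines". No section gives the share of patients who receive any component.

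**The concern.** The rule has a stated purpose, abstraction fidelity, and a stated number. Raw percent agreement serves that purpose poorly for an item that is almost always coded the same way. Two abstractors can agree on most charts because most patients received the component, while both are poor at recognising the patients who did not. Those patients form the comparison group in any component-outcome association. If many of the charts coded as not received are wrong, a real difference shrinks, and a useful component can look unrelated to outcome.

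Two features of the wording add to this. Ten charts give little precision. The phrase "90% agreement on all items abstracted" can also mean that every item must reach 90%, or that all items taken together must; under the second meaning, well-coded items can hide a poor one. It is also not said whether each round uses 10 new charts.

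**Working it through.** The 90% is a chosen criterion, so there is no calculation in the plan to reproduce. What can be checked is how the rule behaves.

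**Inputs from the protocol article.** Threshold 90% and 10 charts (Identify Treatment Received During IETP); about 500 participants (Power and Missing Data).

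**Assumptions.** A yes/no item; true prevalence p between 0.50 and 0.95; in step 3, sensitivity = specificity = 0.95, with errors independent between abstractors and unrelated to outcome.

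**Step 1: precision of 10 charts.** The exact (Clopper-Pearson) 95% interval for 9/10 is 55.5% to 99.7%. For true agreement a, the chance that one item passes one round is 10a⁹(1−a) + a¹⁰. At a = 0.80 this is 0.268 + 0.107 = 0.376.

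**Step 2: what 90% raw agreement means.** If abstractors code independently of the chart, chance agreement is pe = p² + (1−p)², with p the share coded as received. Kappa at 90% raw agreement is (0.90 − pe)/(1 − pe).

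| p | pe | kappa at 90% | one item passes one round by chance |
|---|---|---|---|
| 0.50 | 50.0% | 0.80 | 1.1% |
| 0.80 | 68.0% | 0.69 | 12.1% |
| 0.90 | 82.0% | 0.44 | 43.9% |
| 0.95 | 90.5% | −0.05 | 75.5% |

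Up to p = 0.80 the rule is reasonable. At 0.95, chance agreement alone exceeds the threshold.

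**Step 3: competent but imperfect abstractors.** Raw agreement is 0.95² + 0.05² = 0.905 at every prevalence, so expected agreement is just above the threshold. At p = 0.95:
- Coded received: 0.95×0.95 + 0.05×0.05 = 0.905.
- Chance agreement from these margins: 0.905² + 0.095² = 0.828.
- Kappa: (0.905 − 0.828)/(1 − 0.828) = 0.45.
- Share of not-received codes that are right (NPV): 0.05×0.95/0.095 = 0.50.
- Share of received codes that are right (PPV): 0.9025/0.905 = 0.997.
- Remaining fraction of a true outcome difference: PPV + NPV − 1 = 0.497.
- Both code not received: 0.05×0.9025 + 0.95×0.0025 = 0.0475. Negative agreement: 2×0.0475/(2×0.0475 + 0.095) = 0.50.
- Both code received: 0.95×0.9025 + 0.05×0.0025 = 0.8575. Positive agreement: 2×0.8575/(2×0.8575 + 0.095) = 0.95.

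| p | raw agreement | kappa | NPV | difference retained | negative agreement |
|---|---|---|---|---|---|
| 0.80 | 90.5% | 0.73 | 0.83 | 81% | 0.79 |
| 0.90 | 90.5% | 0.61 | 0.68 | 67% | 0.66 |
| 0.95 | 90.5% | 0.45 | 0.50 | 50% | 0.50 |

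Raw agreement is identical in all three rows, while negative agreement follows the damage. In 500 patients at p = 0.95, 500×0.05 = 25 are true non-receivers, about 48 (500×0.095) are coded as such, and half of those codes are wrong.

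**Step 4: can 10 charts test this at all?** The chance that a set of 10 contains no non-receiver is p¹⁰: 35% at p = 0.90 and 60% at p = 0.95.

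**Step 5: the whole form.** If every item must pass on the same 10 charts, ten independent items coded by chance all pass in 0.4392¹⁰ = 0.03% of rounds at p = 0.90 and 0.7554¹⁰ = 6.1% at p = 0.95. If the 90% is pooled over the ten items, the figures are 2.0% and 65%.

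**The case against.** A reader might infer that abstractors can be cleared by chance and that unreliable data will therefore enter the outcome analysis. The documents do not support that.

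- **Prevalence.** A bundle is not a per-patient rate. The same section expects care to differ with comorbidity and presentation, and the Aim 1 text separates core from peripheral activities. This stands: prevalence near 95% is an assumption, and the problem is confined to items at that level.
- **All items are covered.** On the item-by-item meaning, a whole form coded by chance rarely passes (step 5), and ten items with 80% true agreement all pass together in less than 0.01% of rounds. The 38% in step 1 is a single-item figure. This stands against any claim about the form as a whole. It does not protect against one weak high-prevalence item among well-coded ones, or against masking under pooling.
- **Not all items are yes/no.** Amounts of care are abstracted too, and chance agreement on those would usually be lower. This stands.
- **Other safeguards.** A clinician-informed tool, training, consensus and clinician discussion are planned. The source notes are described as highly accurate, and health system data also cover care during the stay. These lower the risk, but none measures how well non-receivers are recognised.
- **Limited use.** Aim 2 is exploratory and is triangulated with Aim 1. A component with about 25 non-receivers in 500 informs the network weakly even if perfectly coded. This limits the consequence.
- **Appendix not shown.** Multimedia Appendix 12 covers chart abstraction and may say more, so the lack of a later re-check is not held against the plan. The point concerns the rule that the article does state.

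**Conclusion.** The concern holds in limited form. The gate is raw agreement, imprecise at 10 charts, and open on whether it is per item or pooled. For a yes/no component given to about 90-95% or more of patients, passing it does not show that non-receivers are recognised. With 95% sensitivity and specificity, and errors independent of each other and of outcome, an association would keep about 67% of its size at 90% prevalence and 50% at 95%. At 80% prevalence it would keep 81%, and the rule is adequate for less common items. Both the prevalences and the abstractor accuracy are assumptions. The rule fails to exclude unreliable items; nothing shows that the items will be unreliable. The point is minor to moderate: a cheap improvement, not a demonstrated error.

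**What to change.** Restate the stopping rule in Identify Treatment Received During IETP:

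- Apply the criterion item by item, and say so.
- Compute it on the first-pass independent codes, before consensus, cumulated over all calibration rounds.
- For yes/no items, report positive and negative agreement separately. Kappa or a prevalence-robust coefficient can be added, but a fixed kappa cut-off of 0.7 is not advisable: at 95% prevalence, abstractors with 98% sensitivity and specificity reach only 0.69 (agreement 0.961, chance agreement 0.873).
- For amounts of care, use a measure suited to quantities.
- Include calibration charts in which the component was not given.
- Do not use an item with poor negative agreement to label a component ineffective.

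A small double-abstracted sample later on, by the existing team, is optional.

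The cost is a few sentences of procedure and slightly more abstraction and analysis time. Most of the first-pass codes are already produced under the present plan. The downside is that some items may be flagged as unreliable.

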#### Identify Components of IETP Associated With Sustainment and Improvement Trajectories

Outcomes currently identified by operational and clinical stakeholders that are collected at all sites (Tables 3 and 4) will be included in the survey to develop longitudinal outcome trajectories. On the basis of stakeholder feedback, we will also measure and describe community reintegration, employment, retention in the military where relevant, compliance to discharge from the TBI care plan, reasons for difficulty in care plan compliance, and unmet rehabilitation needs. Per operational partners’ request, we will also use VHA and DoD data to identify use relevant to discharge (eg, TBI care plan within primary, mental health, specialty care, or emergency care).

We will use Bayesian network analysis to generate a directed acyclic graph, which probabilistically describes the trajectory of symptoms, care, and outcomes for IETP participants. This network will enable us to explore the contribution of the baseline phenotype to the decision to use a particular treatment course and the contribution of those treatments to the participants’ resulting outcome measures [53]. Using a hill-climbing algorithm scored with the Bayesian information criterion, we will establish directional connections between nodes, called edges, and evaluate the robustness of the edges using bootstrapped samples of the data. We will a priori exclude any implausible directed edges (eg, IETP care cannot lead to precare symptoms). The resulting directed network will have edges between the levels: (1) phenotypes, (2) treatment, and (3) outcomes, while disallowing connections that go from levels 2 to 1 or 3 to 2 or 1. We can allow edges between nodes within the treatment level of the network to better understand the interactions between treatments and to assess how the treatments individually and in combination probabilistically affect patient outcomes. By fitting this model, we can isolate the most probable trajectories between TBI phenotypes and treatments and then determine which treatments have a higher probability of positive long-term outcomes. To gain an understanding of the treatment courses on outcomes, we will present a graphical display of the nodes and edges, the conditional probabilities calculated between nodes that estimate the probability of long-term outcomes given the participants’ IETP components and comorbidity phenotypes, and the robustness measures from bootstrapping.

**Table 3 table3:** Proposed measures for developing trajectory outcomes.

Measure	Baseline	Discharge	Survey	Construct
Mayo-Portland Adaptability Inventory	✓	✓	✓	Ability, adjustment, and participation
Patient Health Questionnaire-9	✓	✓	✓	Depression
PTSD^a^ checklist-5	✓	✓	✓	PTSD
Neurobehavioral Symptom Inventory	✓	✓	✓	Postconcussion symptoms

^a^PTSD: posttraumatic stress disorder.

**Table 4 table4:** Proposed measures for developing trajectory outcomes.

Health system data	Prebaseline	During IETP^a^	After IETP	Construct
Diagnoses	✓	✓	✓	History and emergence of physical or psychiatric comorbidity
Health care use	✓	✓	✓	Type of care received
Medications and procedures	✓	✓	✓	Type of pharmacological or nonpharmacological care

^a^IETP: Intensive Evaluation and Treatment Program.

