**Pre-PEI**			
	Identify and align needs and goals	Work with a team that understands needs and goals from the TBI^a^ and implementation perspective	Ongoing communication and meetings to understand needs and identify priorities
	Engage stakeholders	Prior push to implement not successful	Site representatives recruited to facilitate a bottom-up pull and buy-in from local staff. Input on study design and findings were sought from a stakeholder panel including veterans, service members, VA^b^ and DoD^c^ administrators, and clinicians
	Develop measures and data	Program evaluation data are not standardized and readily accessible	Site representatives recruited to facilitate engagement of stakeholders for data collection. Meetings with PM&R^d^ partners and various stakeholders to identify and prioritize outcomes

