**Data to knowledge (preimplementation stage)**			
	Aim 1: characterize consumer demand	IETP^e^ value from referrals within VA and DoD is unknown	Use of qualitative data collection with patients treated across fully and partially implemented sites
	Aims 1-2: fully characterize the innovation (IETP)	IETP is a black box with poor characterization to duplicate and sustain across systems	Use of qualitative interview technique and quantitative analyses of administrative data sets to identify effective practice core elements and adaptation options
	Aim 2: determine early and late outcomes from IETP	Outcome monitoring has not been the focus of the existing programs	Leverage existing data (eg, IETP data) and collect prospective outcome data to identify measures of success and establish baseline performance at the fully implemented site

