#### Measures and Data Collection Procedures

Data from each IETP participant will be obtained from site leads beginning with Tampa (2015 to present; n=approximately 350). We will obtain identifiers that allow linkage to VA and DoD health system data and create a study crosswalk database behind the VA firewall that includes the encrypted identifier, a study ID, and contact information for interview and survey administration. We will obtain intake and discharge measures from each IETP site. We will assess IETP fidelity based on the IETP characterization table (Multimedia Appendix 1) using a checklist (Multimedia Appendix 2) and chart abstraction focusing on the admission note, admission IETP care plan, discharge TBI care plan, and discharge summary, which are highly accurate in describing the reasons for seeking treatment, baseline status, the type of treatment recommended, the type of treatment received, and outcomes on discharge (Multimedia Appendix 12).

We will also link these IETP data to VA and DoD health system data, as we have done previously [36], to obtain information on physical and mental health, medications, and military demographic data before and after IETP. As approximately 90% (225/250) of participants in the IETP are active duty at the time of treatment with the goal of returning to full duty and operational partner priority outcomes include return to duty or employment, the use of VHA data (eg, Patient Health Questionnaire-9 [PHQ-9] and PTSD checklist-5) is not a feasible approach to long-term outcomes. Therefore, we will conduct a survey using a VA-approved web-based survey software for participants of IETP (2015-2022; approximately 500) using a Modified Dillman Method, which we used in prior VA studies (Multimedia Appendix 13) [37-40]. We will begin a survey of earlier IETP graduates in the first year of the study and send surveys to new graduates 6-9 months post study completion. The final outcome measures included in the survey will be developed in collaboration with stakeholders. The current list of stakeholder-identified measures that are evaluated at intake and discharge include the PHQ-9, PTSD checklist-5, MPAI, and the Neurobehavioral Symptom Inventory.

We will also use VA and DoD health system data to describe health system outcomes such as use, new diagnoses, and adverse outcomes, which will, together with data baseline, discharge, fidelity, and discharge outcomes, be used to develop trajectories of recovery.

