#### Characterize IETP Participants

We will begin characterization with the Tampa site (n=approximately 350) and Richmond site (n=approximately 150), followed by other sites. We will use VA and DoD health system data to characterize preadmission military and sociodemographic characteristics, TBI-related diagnoses (eg, PTSD, pain, and sleep), and medication use (eg, opioids, antidepressants, and sedative hypnotics). We will add data from TBI history and symptom inventories administered at IETP admission to develop mild TBI phenotypes [36,41,42]. This allows the characterization of participants in the IETP and the identification of groups that are likely to have similar courses of care.

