#### Power and Missing Data

The analyses in this aim take an exploratory approach to establishing phenotypes with latent variable mixture models and isolating common trajectories based on Bayesian networks. As such, we do not have a targeted hypothesis with which to power this analysis for minimum detectable effect sizes but rather a model selection approach using the Bayesian information criterion. With 500 participants, we expect that our sample size will be well above the number of nodes in the Bayesian network, which will allow for an accurate estimation of the conditional probabilities in the network [54,55].

We will assess the risk of bias owing to missing data by looking at patterns of missing measurements at each phase of the patients’ trajectories, although we expect most missingness to be postdischarge. Reasons for missing measurements will be tabulated with a focus on differentiating missed measurements for logistical reasons from dropouts or intermittent missingness potentially related to the condition of the patient. If >10% (25/250) of the patients have missing outcome measurements for any of the follow-up measures or if the comparisons of baseline characteristics between patients with missing and nonmissing measurements indicate considerable imbalances, rather than only looking at complete cases, we will apply the structural expectation-maximization algorithm, an imputation method that directly processes data with missing values while fitting the Bayesian network [56]. This method incorporates baseline and follow-up factors beyond the variable being analyzed to account for the dependence of missing data on other factors. TBI history is a primary piece of data required for admission to the program. It is unlikely that any data will be missing for TBI history. However, if >20% (>50/250) of the sample has missing data related to TBI history, the study should be stopped.

### Aim 3

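### The Bayesian network pools 2015–2022 admissions across sites with no level for admission period or site, and the 10% missing-data trigger is worded for follow-up measures only

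*Protocol article*

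**What the plan says.** All references are to the protocol article.

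- **Cohort.** Under Aim 2, Measures and Data Collection Procedures, the survey is planned "for participants of IETP (2015-2022; approximately 500) using a Modified Dillman Method". Intake and discharge measures are to be obtained from each site. Characterize IETP Participants states: "We will begin characterization with the Tampa site (n=approximately 350) and Richmond site (n=approximately 150), followed by other sites".
- **Scores.** Identify Components of IETP Associated With Sustainment and Improvement Trajectories refers to "Outcomes currently identified by operational and clinical stakeholders that are collected at all sites" and places these outcomes in the survey. Table 3, which lists proposed measures, ticks four instruments at baseline, discharge and survey.
- **State of the existing data.** Table 1 lists two challenges identified by the partner: "Program evaluation data are not standardized and readily accessible" and "Outcome monitoring has not been the focus of the existing programs". Its implementation-stage rows add that program innovation was not synchronized and that implementation varied.
- **Network.** The same Identify Components section sets three levels (phenotypes, treatment, outcomes) and disallows backward edges. Admission year and site are not mentioned. The description of treatment received is stratified by phenotype only.
- **Missing data.** Power and Missing Data examines patterns at each phase, "although we expect most missingness to be postdischarge". Structural expectation-maximization replaces complete-case analysis if more than 10% of patients lack outcome measurements on any follow-up measure, or if baseline characteristics differ considerably between patients with and without measurements.

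**The concern.** The network is meant to show which components go with better long-term outcomes. There is no comparison group (Potential Limitations), so every conclusion about a component is a contrast within this pooled cohort. The results are to guide both implementation and deimplementation (Preimplementation Stage; Conclusions).

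In an eight-year, multisite cohort of changing programs, a component may be common at one site or in later years, and outcomes may differ by site or year for other reasons, such as referral mix, staffing or unrecorded changes in care. Period and site are then common causes of treatment and outcome. Left out of the network, their effect can appear as a treatment-to-outcome edge. Bootstrapping does not reveal this, because resampling the same patients reproduces the same confounded association.

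The missing-data plan has a related gap. Structural expectation-maximization fills in values from the variables in the model. If period or site affects both whether a score exists and what it would have been, the scores are not missing at random given phenotype, treatment and outcome alone. Intake scores matter twice, because symptom inventories given at admission also help to build the phenotypes.

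**Working it through.** **1. The plan's own figure.** The plan states: "With 500 participants, we expect that our sample size will be well above the number of nodes in the Bayesian network". The stated site counts give 350 + 150 = 500, which reproduces it. Two sites supply the whole total although five are in scope, so the contributions of the other three are not given. The plan sets no alpha, power or effect size, so there is no sample-size formula to check.

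**2. Size of period confounding (illustration; all inputs assumed).** Take two equal halves, early and late. The component has no effect. It is used in 20% of early and 80% of late patients. Good outcomes occur in 40% of early and 55% of late patients. All scores are available.

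- Good outcome among users: (0.2 × 0.40 + 0.8 × 0.55) / (0.2 + 0.8) = 0.52
- Good outcome among non-users: (0.8 × 0.40 + 0.2 × 0.55) / (0.8 + 0.2) = 0.43
- Spurious difference: 0.52 − 0.43 = 0.09, or 9 points

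With milder use (30% early, 70% late) and the same outcomes:

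- Users: 0.3 × 0.40 + 0.7 × 0.55 = 0.505
- Non-users: 0.7 × 0.40 + 0.3 × 0.55 = 0.445
- Spurious difference: 6.0 points

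**3. Does uneven score coverage cause this?** Let a share c of early patients and all late patients have a recorded score, and analyse observed cases only. For the first set of inputs:

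- Users: (c × 0.2 × 0.40 + 0.8 × 0.55) / (c × 0.2 + 0.8)
- Non-users: (c × 0.8 × 0.40 + 0.2 × 0.55) / (c × 0.8 + 0.2)

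| Early coverage c | Users | Non-users | Difference (points) |
|---|---|---|---|
| 100% | 0.520 | 0.430 | 9.0 |
| 50% | 0.24/0.45 = 0.533 | 0.135/0.30 = 0.450 | 8.3 |
| 25% | 0.23/0.425 = 0.541 | 0.095/0.20 = 0.475 | 6.6 |
| 0% | 0.550 | 0.550 | 0 |

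The milder inputs give 6.0, 5.4 and 4.1 points at 100%, 50% and 25% early coverage. If period affects only coverage, or coverage and component use but not outcome, the difference is 0 at every coverage tried (25% to 100%). The spurious difference thus comes from period as an omitted common cause, and it shrinks as early scores become scarcer.

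**4. How much early missingness would matter for the trigger (assumed even accrual).** 2015–2022 is 8 years, so 500 / 8 = 62.5 patients a year.

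- One early year with no scores: 1/8 = 12.5%, already above a 10% limit.
- Two years at half coverage: 2 × 0.5 / 8 = 12.5%.
- Two years with none: 2/8 = 25%, leaving 375.
- Four years with none: 4/8 = 50%, leaving 250.

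The plan does not say which of these, if any, applies. As worded, an intake-score gap of this size would not clearly set off the 10% rule. The plan also writes 10% as 25/250, whereas 10% of the 500 used for the network is 50.

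**The case against.** The strongest reply has four parts.

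- **The article is condensed and gives no full node list.** Period or site might appear in an analysis plan not shown. This limits what can be said about the final model. But the article does fix the network's levels and the direction of its edges, and period and site belong to none of the three. The point is about that stated structure.
- **The missing-data plan already does a good deal.** It looks at every phase, tabulates reasons, separates logistical ones, and can switch methods on baseline imbalance. This stands: an instrument not yet in use would fall naturally under logistical reasons. It does not put period or site into the model, and the numeric trigger still names follow-up measures.
- **Program change is partly captured**, because components received are abstracted for each patient. This also stands, but it records what was given. It does not account for other reasons why outcomes differ between years or sites.
- **The analysis is declared exploratory.** That excuses the absence of a power calculation. It does not protect component conclusions that feed deimplementation.

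A reader might go further and infer that the plan assumes intake and discharge scores for every 2015–2022 patient, or that outcomes went unmonitored. The documents do not support either. The sentence containing "Outcomes currently identified by operational and clinical stakeholders that are collected at all sites" selects survey content and speaks of the present. Table 3 is a list of proposed measures, and the plan concedes that some missingness precedes discharge. Table 1 says that monitoring was not the focus, which is weaker than saying there was none. Aim 1 sampling also treats the discharge Mayo-Portland score as an outcome across all five sites.

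**Conclusion.** The point holds as one about omitted common causes and a narrowly worded missing-data rule. The stated network has no level for admission period or site, although it pools 2015–2022 admissions from programs that changed at different times. Structural expectation-maximization cannot condition on what is not in the model. The expectation that missingness falls mostly after discharge is given without a reason specific to retrospective scores from unstandardized site data.

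The size cannot be derived from the documents. With use and outcome both differing by period as assumed, a null component shows 6 to 9 points at full coverage, and less as early coverage falls. If period and site affect only one of the two, there is no such bias.

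Two further inferences should be resisted. That score coverage depends on admission era is a possibility to check: no instrument start date and no coverage by year or site is given, and unstandardized data could equally mean differences between sites. The 9-point figure is not a measure of harm from missing scores, since it assumes that none are missing.

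**What to change.** 1. Add admission period and site to the network as root (level 0) nodes that may point to phenotype, treatment and outcome, and that receive no edges. The structural expectation-maximization step then conditions on them too.
2. Before fitting, tabulate availability of each of the four instruments at intake and at discharge, by site and admission year. Count an instrument not yet in use as its own reason for missingness.
3. Apply the 10% trigger to intake and discharge scores as well as to follow-up measures, and include admission year and site in the comparison of patients with and without scores.
4. Use restriction to site-years with high coverage as a sensitivity analysis only, since it may discard early patients.

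The cost is one table and two nodes, from data the project already plans to hold, plus extra parameters. A two-level period as parent doubles a node's conditional table, and five sites multiply it by up to five. The Bayesian information criterion penalizes this and keeps only supported edges. If some sites are too small, they can be grouped, with the grouping fixed before outcomes are seen.
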